### Participant timeline

Participants who meet the inclusion criteria will be reached by research coordinator for possible enrollment. Participants will be enrolled in the study after consenting and before receiving a RFN of the CMBN. The goal of this trial is to demonstrate non-inferiority of the end-on technique as compared to the conventional parallel technique for RFN of the CMBN. The baseline study questionnaires will be completed within 4 weeks before the study intervention. Baseline data on sleep and physical activity will also be collected using actigraphy over 1 week prior to the trial intervention and for at least 1 week prior to the follow-up at 1 month after the intervention. Routine scheduled study follow-ups will occur at 1, 3, 6, and 12 months after the study interventions, at which times all follow-up measures will be obtained (Table 2, Fig. 1). The follow-up at 1 and 3 months will be in-person whereas the follow-ups at 6 and 12 months may be virtual (video/phone) to assess trial-relevant outcomes.

### Sample size

The sample size was calculated using the Statistical Package for the Social Sciences (SPSS, IBM SPSS Statistics) software. A sample size of 72 participants (36 in each treatment group) will provide 80% power to detect a difference (inferiority margin), at 3 months after the intervention, in the mean NRS pain intensity scores (0–10 scale) between the two treatment groups being less than or equal to 1 point, given a standard deviation (SD) of 1.7 at the 0.05 significance level (alpha) using a two-sided two independent sample *t*-test. To satisfy both the non-inferiority and superiority hypothesis, we plan to recruit a total of 80 participants to account for a presumed 10% dropout rate. The sample size calculations and the assumptions underlying it are based on data published on RFN of nerves supplying other axial joints (lumbar facets, sacroiliac) for the relief of spinal pain [12, 13]. The chosen non-inferiority margin of less than or equal to 1 point (10%) is reasonable because a minimal clinically important difference in pain scores for a treatment to be considered efficacious is 2 points or 30% [14]. A non-inferiority study is justified to compare the end-on and parallel RFN lesions because similar efficacy is expected but there may be a lower incidence of adverse effects (e.g., patient discomfort) and better resource utilization (e.g., faster procedure time, lower radiation dose) with the end-on RFN technique.

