**Methods:**

A multicentre randomized, non-inferior, active comparator-controlled trial will be conducted with two parallel groups and blinding of participants and outcome assessor. The study will include 72 adults with chronic neck pain secondary to facet joint disease who are candidates for RFA of the CMBN. Participants will be randomized to either the conventional parallel or the end-on approach in a 1:1 ratio. The intensity of pain and pain-related domains (function, quality of life, sleep, adverse effects of the interventions, analgesic intake) will be measured at 1, 3, 6, and 12 months after the procedure.

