### Statistical methods

A statistician will be consulted to assist in data analysis and interpretation. Descriptive information for the sample’s study measures will include frequency distributions or proportions for categorical variables and means (standard deviations) or medians (interquartile ranges) (if non-normally distributed) for the continuous variables. To compare data between the two groups, categorical outcomes will be analyzed with the chi-square test and continuous variables will be analyzed with independent *t*-tests (or Wilcoxon rank sum test, as appropriate). A two-sided *p*-value of < 0.05 will be considered statistically significant. Both intention-to-treat (based on study arm allocation) and per-protocol (based on the participants who adhered to the study protocol and provided data at study outcome time points) analysis will be performed and reported.

Correlation between reduction in pain and improvement in function will be evaluated with a longitudinal model of changes from baseline to 3-month, 6-month, and 12-month follow-ups. An intention-to-treat strategy will be used for all analyses. Differences in treatment effects and 95% confidence intervals for pain and secondary outcome scores will be calculated using chi-square and odds ratios for dichotomous variables, and ANOVA (with *t*-tests for pairwise comparisons) and Mann–Whitney for continuous variables, as indicated. A set of logistic regression models for categorical outcome at 3 months will be created using variables hypothesized to have an effect on treatment (gender, intensity of pain, nature of injury), as well as those found to have a *p*-value less than 0.20 in univariate analysis. A secondary analyses based on data from participants who undergo unilateral versus bilateral RFN with each of the two study treatments is also planned. Missing data will be imputed using the “last observation carried forward” approach if at least 80% of the outcome data is available for the participant. All analyses will be performed using the SPSS program.

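### At the stated two-sided 0.05 level, 36 per arm gives about 69–70% power for the 1-point margin, not 80%; the 72 fits a one-sided 0.05 level that the protocol article never declares

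*Protocol article*

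**What the plan says.** The Sample size section sets out the calculation for mean NRS pain at 3 months, one of two primary outcomes: "A sample size of 72 participants (36 in each treatment group) will provide 80% power to detect a difference (inferiority margin"), with the margin put at 1 point, "given a standard deviation (SD) of 1.7 at the 0.05 significance level (alpha) using a two-sided two independent sample" t-test. It defends the margin: "The chosen non-inferiority margin of less than or equal to 1 point (10%) is reasonable".

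It then gives the recruitment target: "To satisfy both the non-inferiority and superiority hypothesis, we plan to recruit a total of 80 participants", and the same sentence cites a 10% dropout allowance.

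The Statistical methods section sets significance at a two-sided p-value below 0.05 and adds: "Differences in treatment effects and 95% confidence intervals for pain and secondary outcome scores will be calculated". It does not say which interval bound decides non-inferiority. No one-sided 0.05 test and no 90% interval appears anywhere in the article.

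The Abstract (Methods) says: "The study will include 72 adults with chronic neck pain secondary to facet joint disease". The Discussion gives eighty.

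**The concern.** The Sample size section prints every input needed to check its own claim: number per arm, margin, SD, alpha, sidedness and power. These cannot all be true together. The analysis section repeats the two-sided level, so the label cannot be dismissed as a slip in one sentence.

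Two things are at stake. The first is the chance that the trial reaches its main conclusion when the techniques are in fact equivalent. The second is the decision rule. With the sample size fitting one alpha and the stated analysis using another, the choice between a 90% and a 95% interval could be made after the data are seen, and it could settle the result.

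The mention of a superiority hypothesis in the recruitment sentence also suggests that the 80 was sized for more than dropout.

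**Working it through.** **Inputs (Sample size section).** n = 36 per arm; margin M = 1 NRS point; SD = 1.7; alpha 0.05, two-sided; claimed power 80%; dropout 10%. The true difference is not stated. I take it as 0, in line with the section's expectation of similar efficacy.

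**Standard error.** SE = SD × √(2/n) = 1.7 × √(2/36) = 0.4007, so M/SE = 2.496.

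**Reproducing the plan's figure.** Sample size per arm by normal approximation: n = 2(z_α + z_β)² SD² / M².
- One-sided 0.05: 2 × (1.645 + 0.842)² × 1.7² / 1² = 35.7, rounded up to 36. This matches the protocol's 36 per arm.
- Two-sided 0.05 (one-sided 0.025): 2 × (1.960 + 0.842)² × 1.7² / 1² = 45.4, rounded up to 46.

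With the t distribution, the smallest n for 80% power is 37 per arm (one-sided 0.05) and 47 per arm (two-sided 0.05).

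**Power at a given n.** Normal approximation: Φ(M/SE − z_α). The t column uses the noncentral t with 2n − 2 degrees of freedom.

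| n per arm | Level | Normal | Noncentral t |
|---|---|---|---|
| 36 | two-sided 0.05 (95% CI) | Φ(2.496 − 1.960) = 70.4% | 69.2% |
| 36 | one-sided 0.05 (90% CI) | Φ(2.496 − 1.645) = 80.3% | 79.6% |
| 40 (all 80 complete) | two-sided 0.05 | 74.9% | 73.8% |

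**Does the reading matter?** Taken literally as a two-sided test to detect a true difference of 1 point, the calculation gives the same 69–70%. It is numerically the same problem as non-inferiority with true difference 0 and a one-sided 0.025 bound. An equivalence reading (two one-sided tests, margin ±1) gives less: about 61% at 0.05 per side and 41% at 0.025 per side (normal approximation). For 36 per arm to reach 80% at two-sided 0.05, the SD would have to be about 1.49 or the difference about 1.14. Neither is stated.

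**Consequence at the 95% bound.** 100% − 69.2% = 30.8%, so about 31% of trials of a truly equivalent technique would fail on mean NRS, against the 20% implied by the claim.

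**Numbers needed for 80% at two-sided 0.05.** 46–47 per arm is 92–94 evaluable. With 10% dropout, 92/0.9 = 102.2 and 94/0.9 = 104.4, so about 103–105 recruited.

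**The 80 recruits.** 72/0.9 = 80 exactly. The extra 8 are used up by dropout. For superiority with 36 per arm, the difference detectable with 80% power at two-sided 0.05 is about 1.14 points (noncentral t).

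**The case against.** The best defence is that the 72 is a sound non-inferiority sample size at one-sided 0.05 and only its label is wrong. The article never names the bound that decides non-inferiority, and an analysis plan that is not shown may do so. If it used a one-sided 0.05 bound, 72 evaluable participants would be adequate. This stands as far as it goes: the 31% failure rate holds only if the 95% bound decides. It does not rescue the printed statement, which pairs 80% power with a two-sided 0.05 test. No separate document can make that arithmetic true.

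A reader might go further and infer that the 72 was certainly derived at one-sided 0.05. The software inputs are not shown, so the figure is only consistent with that. With the t-test that the section names, one-sided 0.05 gives 79.6%, and 37 per arm would be needed to reach 80%.

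A reader might also expect a baseline-adjusted analysis to recover the lost power. The Statistical methods section plans t-tests, rank tests or ANOVA for continuous outcomes and names no baseline-adjusted model for NRS, so no such gain can be claimed from the document.

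On superiority, the sentence is muddled and may mean only that the same participants serve both tests. Testing superiority after non-inferiority needs no extra participants to be valid. What stands is that the 80 adds nothing for superiority beyond replacing dropouts.

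The 72 and the 80 could be read as rival sample sizes. The Sample size section reconciles them as the number before and after the dropout allowance, so the difference is one of wording.

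**Conclusion.** The power statement is wrong as written. With the protocol's own inputs, 36 per arm gives about 69% (t) to 70% (normal) at two-sided 0.05, roughly 10 percentage points below the claim. No choice of approximation closes that gap, and even 80 completers would give only about 74–75%. The stated figure is recovered, to within rounding, only at one-sided 0.05, a level that the article does not declare and that its analysis section does not use.

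The result assumes a true difference of 0, SD 1.7 and an unadjusted comparison of means, and it concerns mean NRS only. It does not address the responder proportion, the other primary outcome. It does not show that the trial must enrol more participants: a declared one-sided 0.05 rule would fit the planned size.

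**What to change.** Before unblinding, fix one alpha for both the sample size and the non-inferiority decision, and name the interval whose bound decides. Either option is coherent:

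- Keep the two-sided 95% interval (one-sided 0.025) and restate the power of 72 evaluable participants for the 1-point margin as about 69–70%.
- Declare one-sided 0.05 with a 90% interval for the non-inferiority decision, state power of about 80%, and amend the analysis section to match.

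Correct the clause that ties 80 recruits to the superiority hypothesis. Either remove it, or say that the 80 allows for dropout only and that 72 evaluable participants give 80% two-sided power only for a difference of about 1.14 points.

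As a side note, use 80 recruited and 72 evaluable consistently, including in the Abstract.

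The cost is wording in the protocol and, where it repeats these figures, the registry entry. No further participants are required. Under the first option the stated power becomes less favourable; under the second, the non-inferiority decision rests on a less strict level.

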### Hypotheses

The primary hypotheses for this non-inferiority trial are that end-on lesioning for RFN of the CMBN is non-inferior to the parallel conventional technique for its impact on the intensity of pain relief and the proportion of patients with a positive analgesic response at 3 months after the intervention in patients with chronic, moderate-to-severe neck pain in the context of cervical zygapophyseal joint syndrome. The secondary hypotheses are that end-on lesioning for RFN of the CMBN is non-inferior to the parallel conventional technique for its impact function, quality of life, sleep, adverse effects of the interventions, analgesic intake at specified time points within 1 to 12 months after the interventions in patients with chronic, moderate-to-severe neck pain in the context of cervical zygapophyseal joint syndrome.

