### Trial design

The EndParl study is designed as a prospective, multicentre, active comparator-controlled, non-inferiority randomized trial with two parallel groups and blinding of participants and outcome assessors. Randomization will occur on the day of the procedure and will be done to one of two arms on a 1:1 allocation basis. The randomization sequence will be computer-generated, and allocation concealment will be ensured by sequentially numbered, sealed opaque envelopes. This process will be carried out by an independent research coordinator, who will not be involved in the recruitment process or conduct of the trial. An unblinded physician will do the procedure but they will not be involved in assessing the outcomes. A blinded member of the research team will perform follow-up outcome assessments. Treating physicians, participants, close contacts, trial coordinators, and primary outcome analysts will be blinded to treatment allocation.

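### The recruitment target of 80 is said to serve a superiority hypothesis as well as non-inferiority, but no such hypothesis is stated and 80 is only 72 inflated for dropout

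*Protocol article*

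**What the plan says.** The Sample size section of the protocol article first sets the evaluable number: "A sample size of 72 participants (36 in each treatment group) will provide 80% power to detect a difference (inferiority margin"), for a difference in 3-month mean NRS "between the two treatment groups being less than or equal to 1 point, given a standard deviation (SD) of 1.7", and "at the 0.05 significance level (alpha) using a two-sided two independent sample" *t*-test. It then moves to recruitment: "To satisfy both the non-inferiority and superiority hypothesis, we plan to recruit a total of 80 participants", and that sentence ends by giving a presumed 10% dropout as the reason for the number. Later in the section, the choice of a non-inferiority design is defended on the ground that "similar efficacy is expected", with possible gains in adverse effects and resource use.

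The Hypotheses section frames both the primary and the secondary hypotheses as being that "end-on lesioning for RFN of the CMBN is non-inferior to the parallel conventional technique". Trial design and Participant timeline likewise describe a non-inferiority trial with a non-inferiority goal. The word superiority, as a hypothesis of this trial, occurs only in the Sample size sentence.

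**The concern.** The sentence gives the number 80 a second function: it is said to be enough for a superiority hypothesis. Two things make that doubtful. No superiority hypothesis is set out for the number to satisfy, and the step from 72 to 80 looks like a dropout allowance and nothing more.

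The stake is in how results are read. Statistical methods plans two-sided tests of difference at p < 0.05 for the between-group comparisons. It does not call them superiority tests, but a reader of the Sample size sentence could take the test on NRS to be a planned and adequately powered one. A significant result could then be presented as a prespecified superiority finding. A non-significant one could be taken as fair evidence that there is no advantage.

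**Working it through.** **Inputs.** From Sample size: 36 evaluable per arm, 80% power, 1 point on the NRS, SD 1.7, alpha 0.05 with a two-sided *t*-test, 10% dropout. From Trial design: 1:1 allocation. Not given anywhere: a superiority endpoint or effect. The power figures in steps 3 to 5 therefore assume that superiority means a lower 3-month mean NRS with the end-on technique.

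**1. The plan's 72.** For non-inferiority with margin 1 and true difference 0, the normal approximation gives n per arm = 2 × SD² × (z_alpha + z_power)² / margin².
- One-sided 0.05: 2 × 2.89 × (1.645 + 0.842)² = 35.7, so 36 per arm and 72 in total. Power at 36 per arm is 80.3% (normal) or 79.6% (noncentral *t*).
- Two-sided 0.05: 2 × 2.89 × (1.960 + 0.842)² = 45.4, so 46 per arm and 92 in total (47 and 94 by noncentral *t*).

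The figure of 72 therefore reproduces as a one-sided 5% non-inferiority calculation. It does not reproduce under the two-sided 0.05 test that the section names.

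**2. From 72 to 80.** 72 / (1 − 0.10) = 80 exactly. The dropout allowance accounts for the whole increase.

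**3. Superiority power at the section's only design difference.** The standard error of the difference is SD × √(2/n).
- 36 per arm: 1.7 × √(2/36) = 0.401; noncentrality 1/0.401 = 2.50; critical *t* on 70 df = 1.994; power 69.2% (normal approximation 70.4%).
- 40 per arm, no dropout: 1.7 × √(2/40) = 0.380; noncentrality 2.63; critical *t* on 78 df = 1.991; power 73.8% (normal approximation 74.9%).

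Reaching 80% at 1 point would take the 92 to 94 evaluable participants of step 1. At 10% dropout that is 92/0.9 = 102.2, so 103 recruited, or 94/0.9 = 104.4, so 105 recruited.

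**4. Difference detectable with 80% power (two-sided 0.05, noncentral *t*).** 1.14 points with 36 per arm and 1.08 with 40. The normal approximation gives 1.12 and 1.06.

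**5. Power at other true advantages, 36 per arm.**

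| True advantage (NRS points) | Power |
|---|---|
| 0.75 | 45% |
| 1.00 | 69% |
| 1.25 | 87% |
| 1.50 | 96% |
| 2.00 | over 99% |

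**6. Text against text.** Sample size speaks of a superiority hypothesis. Hypotheses has none, at either primary or secondary level. Sample size also rests the design on an expectation of similar efficacy, which is not an effect for which a superiority test can be sized.

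**The case against.** The strongest reply is that this is a stray phrase. The 72 and the 80 are linked correctly, so there is no slip in the dropout arithmetic. Neither the trial's goal nor the planned cost-effectiveness follow-on depends on superiority. Testing superiority after non-inferiority has been shown costs no alpha, and the testing order is something that an analysis plan, not shown here, may settle. All of this stands, and the missing testing order is not counted as a fault. An analysis plan could not, however, turn 80 into a number derived for superiority.

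A reader might go further and infer that the trial has no power for superiority. The documents do not support that. They set no superiority effect, so the power is unspecified. It exceeds 80% above about 1.14 points and 99% at 2 points, the clinically important difference that Sample size cites. That section uses the 2 points to justify the margin, though, and not as an expected advantage. Pointing to the very low rejection rate at a true difference of zero would prove nothing either, because a superiority test has only its alpha there at any sample size.

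The endpoint is also open. The gains that the section hopes for are in adverse effects, discomfort, procedure time and radiation dose, so superiority may have been meant for one of these. The Hypotheses section frames adverse effects as non-inferiority, which weakens that reading without excluding it. The NRS power figures are conditional for this reason.

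**Conclusion.** The point holds in a limited form. The article says that 80 participants serve a superiority hypothesis, but it states no such hypothesis, endpoint, effect or power, and 80 is exactly 72/0.9. Taken as superiority on 3-month mean NRS at 1 point, SD 1.7 and two-sided 0.05, power is about 69% with 36 evaluable per arm and 74% with 40, against the 80% stated for the design. A true advantage of about 1.14 points (1.08 with 40 per arm) is needed for 80%. These figures rest on the plan's SD and on the assumed endpoint.

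This is an unsupported statement about what the sample size achieves. It does not undermine the non-inferiority objective. Any rewording does have to deal with the alpha, because 72 gives about 80% non-inferiority power only at one-sided 0.05. The point deserves correction because the remedy is cheap and the sentence could otherwise be cited for a superiority claim.

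**What to change.** Remove the reference to superiority from the Sample size sentence. State in its place that 80 participants will be recruited so that about 72 are evaluable after 10% dropout, and that the trial is sized for non-inferiority on 3-month mean NRS only. Give the assumptions: margin 1 point, SD 1.7, true difference 0, about 80% power at one-sided alpha 0.05. Reconcile this with the two-sided 0.05 test now named there, since at that level the same inputs need 92 to 94 evaluable. Saying only that 72 is sized for non-inferiority would leave that mismatch in place.

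If superiority is to be kept, name its endpoint and state that it is tested only once non-inferiority has been shown. If the endpoint is mean NRS, add that 36 per arm gives 80% power only for a true advantage of about 1.14 points at two-sided 0.05.

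Removing or qualifying the superiority claim is a change of wording and needs no extra patients. The cost is giving up a claim that the design does not support.

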### Recruitment

#### Feasibility of recruitment

Participants will be recruited from the Comprehensive Integrated Pain Program – Interventional Pain Service (CIPP-IPS) clinic at Toronto Western Hospital and the Pain Medicine Clinics affiliated with the Division of Pain Medicine at the University of Toronto. Around 15 patients undergo RFN of the CMBN every month at the study sites. Assuming a study enrollment rate of 50%, we should be able to recruit 7 to 8 participants every month. We expect to enroll the required sample size for the study over 9 to 12 months. There are two other academic pain centers and two community pain clinics in the Toronto area that may be approached to become study enrollment sites if the proposed enrollment is lower than anticipated.

#### Recruitment strategy

The Principal Investigator will introduce the trial to physicians and surgeons who refer patients with neck pain secondary to cervical facet joint syndrome the study sites. The referring physicians and surgeons will be encouraged to refer patients with chronic neck pain who meet the inclusion criteria.

